### Randomization and blinding

A 1:1 randomization will be performed and patients will be assigned with a randomization number. In case there are dropouts, these patients will be replaced and the new patients will be assigned in an identical manner. If a patient drops out of the study at month 6 due to his/her own decision, the patient data will be removed from the trial completely, including any data generated prior to the withdrawal. If a patient passes away during the first 6 months, the data will be used. If the urine probes reveal that a patient from the broccoli sprouts group did not consume the broccoli sprouts daily or if a patient from the placebo group had a high dietary intake of isothiocyanates, the data from these patients will not be used, but the patient will be replaced by a new patient, even if a patient drops out between months 9 to 12. This case will extend the duration of the study. Randomly generated numbers will be allocated to the two groups in balanced permuted blocks using a number generator (validated software, SAS). In order to avoid any possibility of predicting the group allocation, the length of the blocks will be fixed in a separate document and this information will be withheld from the study site. A data sheet that links the group allocation with the randomized number of the patient will be sealed in pre-produced, non transparent envelopes labeled with the arbitrary patient numbers and these envelopes will be used in consecutive order. In order to be able to perform a retrospective control of the compliance to randomization, basic patient data, including the day on which the patient’s number was assigned, will be noted on the data sheet. After completing the trial, all unopened envelopes will be delivered to the data management center for comparison to the allocated, randomized patient numbers and examination and evaluation of the thoroughness of the trial.

The investigators, patients, and assessors of the POUDER trial will be blind to the patients’ study treatment courses. The principal investigator (PI) will be provided with a set of sealed envelopes containing information on patients’ trial drugs, one for each patient number. These envelopes are to be opened only under imperative circumstances (medical indication to know the substance in use by the subject).

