### Data management and statistical analysis

The trial investigator or a designated representative (sub-investigator) will document all data acquired during the trial in a case report form (CRF) on the day of the routine visit. All missing or inconsistent data will be reported and inferred. Upon completion, all CRFs must be officially reviewed and signed by either the investigator named in the trial protocol or by a designated sub-investigator. In order to assure the highest data quality and accurate transfer from the CRF to the database, a double data-entry method will be performed. After completing the trial, the PI will retain the original CRFs.

Totality, validity, and plausibility of the data will be examined by validating programs that will generate queries that must be clarified by the investigator. All findings, both clinical and overall survival, imaging of disease stages, quality of life, and biochemical analyses will be noted in the subject’s CRF.

As this is a pilot study, no sample size calculation was performed. A sample size of 20 patients per study group has been deemed sufficient for the study objectives. The sample size of 20 patients per group is speculative at this time and it is based on comparable patient numbers used in similar ongoing and recently completed patient studies with broccoli sprout extracts. For example, the Pittsburgh pilot study evaluating sulforaphane in atypical nevi-precursor lesions enrolled 18 patients (http://clinicaltrials.gov/ct2/show/NCT01568996?term=NCT01568996&rank=1) and another study performed at OHSU Knight Cancer Institute for examination of sulforaphane in treating patients with recurrent prostate cancer (http://clinicaltrials.gov/ct2/show/record/NCT01228084?term=sulforaphane&rank=1) enrolled 20 patients.

Depending on data characteristics, descriptive statistics of the monitored parameters will be presented as mean values and SD or median values and IQR. Descriptive *P*-values of the *t*-test or the Mann-Whitney *U*-test comparing the treatment groups will be given, together with the corresponding 95% CI. Categorical parameters will be presented as relative and absolute frequencies, and comparisons will be performed using the Fisher exact test.

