Survival curves will be constructed using the Kaplan-Meier estimator. The descriptive *P*-value of the log-rank test will be used to compare the survival curves of the treatment groups. Estimated median survival times and the one-year survival rates with 95% CI will be given.SAS software (Release 9.1, SAS Institute, Inc. Cary, NC, USA) and Microsoft Office Excel 97® (Redmond, Washington, USA) will be used for the statistical analysis and graphical presentations.

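### Erasing patients who withdraw at month 6, while keeping early deaths, pulls the survival curve down to month 6 and removes feasibility and safety records

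*Protocol article*

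**What the plan says.** The rule stands in the protocol article under Methods/Design, Randomization and blinding. Its trigger is "If a patient drops out of the study at month 6 due to his/her own decision", and its consequence is that "the patient data will be removed from the trial completely, including any data generated prior to the withdrawal". The next sentence treats death differently: "If a patient passes away during the first 6 months, the data will be used". Drop-outs are also replaced: "In case there are dropouts, these patients will be replaced and the new patients will be assigned in an identical manner".

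The section Data management and statistical analysis plans survival results from what remains: "Survival curves will be constructed using the Kaplan-Meier estimator", with median survival and one-year rates, and "The descriptive *P*-value of the log-rank test will be used to compare the survival curves of the treatment groups". Nothing in the article exempts survival or safety data from the erasure.

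Three other places bear on the rule. Trial objectives makes the practicability of taking 15 capsules a day the principal objective. The end of Trial interventions has the last visit bring together all efficacy and safety data. Adverse and serious adverse events has every adverse event recorded and followed.

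**The concern.** Whether a patient counts from day 0 depends on something that happens six months later and that only a survivor can do. Each patient erased at month 6 has contributed six months alive; each patient who died earlier stays. Kaplan-Meier estimation is built to use such a patient up to the date of leaving, so the loss is avoidable.

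Two things are at stake. The survival estimates feed the hypothesis for a confirmatory trial (Outcome measures; Discussion), and they would carry a bias created by the data rule. More important for a feasibility trial, a patient who chooses to stop is evidence on the principal objective, yet that patient's diary, urine, adverse-event and quality-of-life data leave the analysis.

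This is a stated rule, not a detail left to an analysis plan. A later plan cannot analyse data that have been removed.

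**Working it through.** **Plan's own figure.** The article states that "As this is a pilot study, no sample size calculation was performed". It gives 20 per group, and 2 × 20 = 40 agrees with the total. There is no drop-out rate to reproduce.

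**Inputs.** Median survival of 4 to 6 months (Background, for pancreatic ductal adenocarcinoma generally). Follow-up of 12 months (Trial interventions). Assumed here: exponential survival, and a share q of six-month survivors who withdraw at month 6 and are erased.

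**Counting example.** Of 20 patients, suppose 10 die before month 6 and 3 of the 10 survivors withdraw. Kept and censored: S(6) = 10/20 = 50%. Erased: S(6) = 7/17 = 41%.

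**General formula.** Let w = q·S(6). After erasure:
- S(6) becomes (S(6) − w)/(1 − w).
- S(12) becomes that value times S(12)/S(6), if withdrawers and stayers have the same later prognosis.
- Mortality at any t ≤ 6 becomes F(t)/(1 − w), which exceeds F(t).

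For a 5-month median, S(6) = 0.5^(6/5) = 0.435. With q = 30%, w = 0.131, so S(6) becomes (0.435 − 0.131)/(1 − 0.131) = 0.350, and S(12) becomes 0.350 × 0.435 = 0.153.

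| True median (months) | q | S(6) true → erased | S(12) true → erased | Median after erasure (months) |
|---|---|---|---|---|
| 4 | 10% | 35.4% → 33.0% | 12.5% → 11.7% | 3.8 |
| 4 | 30% | 35.4% → 27.7% | 12.5% → 9.8% | 3.4 |
| 5 | 10% | 43.5% → 41.0% | 18.9% → 17.8% | 4.7 |
| 5 | 30% | 43.5% → 35.0% | 18.9% → 15.3% | 4.1 |
| 6 | 10% | 50.0% → 47.4% | 25.0% → 23.7% | 5.6 |
| 6 | 30% | 50.0% → 41.2% | 25.0% → 20.6% | 4.8 |

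**Replacement does not cure it.** In a simulation with 20 analysed per arm and erased patients replaced (4,000 runs, 6-month median, q = 20%), mean S(6) and S(12) were 44.6% and 22.3%, against a true 50.0% and 25.0%. With the same patients censored instead, they were 49.8% and 25.2%.

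**When the one-year direction changes.** Let withdrawers' hazard after month 6 be h times that of stayers. With s = 0.435 for stayers' survival from month 6 to 12, true S(12) = S(6)·[(1 − q)s + q·s^h]. For a 5-month median and q = 30%:
- h = 1: true 18.9%, erased 15.3%.
- h = 3: true 0.435 × (0.7 × 0.435 + 0.3 × 0.0825) = 14.3%, erased 15.3%.
- The two agree when s^h = (1 − q)·s·S(6)/(1 − w) = 0.7 × 0.4353²/0.8694 = 0.1526, so h = ln 0.1526 / ln 0.4353 ≈ 2.3.

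**Between arms, no treatment effect, 5-month median.** Withdrawal of 30% against 10% shows S(6) of 35.0% against 41.0%, a gap of 6 points. With 20 per arm its standard error is √(0.35 × 0.65/20 + 0.41 × 0.59/20) ≈ 0.15. Simulated log-rank rejection at two-sided 5%, over medians of 4 to 6 months:
- 20% against 20%: 5.4% to 5.6%
- 30% against 10%: 6.4% to 7.1%
- 30% against 0%: 7.6% to 7.9%
- 50% against 0%: 14% to 16%

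Censoring the same patients gave 4.9% to 6.3% in the patterns simulated (20% against 20%, 30% and 50% against 0%, 50% against 10%).

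**Feasibility and safety.** No arithmetic is needed. A rule that removes everything recorded on a voluntary leaver cannot stand beside an objective of testing whether intake is possible, or beside the intention to compile all efficacy and safety data.

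**The case against.** The strongest reply is that this is a feasibility pilot: survival is documented as an additional item, P-values are descriptive, and with 20 per arm a 6-point gap is well inside sampling error. That stands, and it limits the weight of the survival argument. It does not touch the lost feasibility and safety records.

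Several stronger readings are tempting but are not supported:

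- *Survival is understated at every time, whatever happens.* Through month 6 the direction is certain only if the trigger is withdrawal at month 6. The phrase could also mean up to month 6. In a simulation of that reading (5-month median, 30% of patients given withdrawal times spread evenly over months 0 to 6, hazard tripled afterwards), true S(6) was 36.8% and the erased estimate 38.2%. One-year survival can reverse in the same way. Censoring is then biased upwards too, so none of this defends erasure.
- *A false survival difference will appear.* With equal withdrawal both curves fall and the log-rank test stays near nominal. The 14% to 16% rejection needs an extreme imbalance.
- *Drop-out vanishes from the report.* The article removes patient data, not the count. Withdrawals can still be counted from randomisation numbers, assignment dates and the envelope check, and serious adverse events already reported to the ethics committee remain there.
- *The leavers are mostly people who could not tolerate the capsules.* The article gives no reasons for leaving.
- *Replacement must stop.* The bias shown comes from erasure, not from replacement.

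It may also be said that data protection requires erasure. The article cites the German Federal Data Protection Act, and the consent pages are not shown, so a consent basis cannot be checked. As written, though, erasure follows automatically from dropping out and not from a request to delete.

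**Conclusion.** The rule should be changed. On its literal reading it makes the Kaplan-Meier curve too low through month 6. At every time the curve lies at or below the one obtained by censoring these patients. One-year survival is understated too, unless withdrawers' later hazard is well above that of stayers (about 2.3 times in the 5-month, 30% illustration).

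The direction through month 6 follows from the rule; the size does not. It rests on assumed withdrawal rates, exponential survival and a median quoted for the disease in general, not for patients on palliative chemotherapy who can eat. For 10% to 30% erasure at a 5-month median, six-month survival falls by 2.5 to 8.5 points. Bias between arms arises only with unequal withdrawal and is modest. The separate urine-based exclusions in the same section may push in another direction, so the net bias of all exclusions is not settled here.

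The weightier consequence is the loss of adherence, adverse-event and quality-of-life records, which conflicts with the principal objective.

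**What to change.** Replace the erasure sentence so that:
- data collected up to withdrawal are kept and analysed for all randomised patients;
- survival is censored at the last date known alive;
- stopping capsules is recorded separately from withdrawing consent, and patients who only stop capsules remain in follow-up for survival and adverse events;
- data are erased only where a patient explicitly revokes use of data already collected;
- withdrawals and erasures are reported by arm, with reasons where given.

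If drop-outs are still replaced, the replaced patients stay in the analysis. The new sentence should also say whether it covers withdrawal at the month 6 visit or at any time.

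The cost is small: a change to protocol and consent wording, and some added censoring. That censoring is itself unbiased only if withdrawal is unrelated to later prognosis, which the report should state.

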### Data management and statistical analysis

The trial investigator or a designated representative (sub-investigator) will document all data acquired during the trial in a case report form (CRF) on the day of the routine visit. All missing or inconsistent data will be reported and inferred. Upon completion, all CRFs must be officially reviewed and signed by either the investigator named in the trial protocol or by a designated sub-investigator. In order to assure the highest data quality and accurate transfer from the CRF to the database, a double data-entry method will be performed. After completing the trial, the PI will retain the original CRFs.

Totality, validity, and plausibility of the data will be examined by validating programs that will generate queries that must be clarified by the investigator. All findings, both clinical and overall survival, imaging of disease stages, quality of life, and biochemical analyses will be noted in the subject’s CRF.

As this is a pilot study, no sample size calculation was performed. A sample size of 20 patients per study group has been deemed sufficient for the study objectives. The sample size of 20 patients per group is speculative at this time and it is based on comparable patient numbers used in similar ongoing and recently completed patient studies with broccoli sprout extracts. For example, the Pittsburgh pilot study evaluating sulforaphane in atypical nevi-precursor lesions enrolled 18 patients (http://clinicaltrials.gov/ct2/show/NCT01568996?term=NCT01568996&rank=1) and another study performed at OHSU Knight Cancer Institute for examination of sulforaphane in treating patients with recurrent prostate cancer (http://clinicaltrials.gov/ct2/show/record/NCT01228084?term=sulforaphane&rank=1) enrolled 20 patients.

Depending on data characteristics, descriptive statistics of the monitored parameters will be presented as mean values and SD or median values and IQR. Descriptive *P*-values of the *t*-test or the Mann-Whitney *U*-test comparing the treatment groups will be given, together with the corresponding 95% CI. Categorical parameters will be presented as relative and absolute frequencies, and comparisons will be performed using the Fisher exact test.

Survival curves will be constructed using the Kaplan-Meier estimator. The descriptive *P*-value of the log-rank test will be used to compare the survival curves of the treatment groups. Estimated median survival times and the one-year survival rates with 95% CI will be given.SAS software (Release 9.1, SAS Institute, Inc. Cary, NC, USA) and Microsoft Office Excel 97® (Redmond, Washington, USA) will be used for the statistical analysis and graphical presentations.

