### Outcome measures

Serum levels of the pancreatic tumor markers carbohydrate antigen 19-9 (CA19-9) and carcinoembryonic antigen (CEA), and routinely performed cross-sectional imaging (computed tomography or magnetic resonance imaging), will be monitored and assessed as parameters for evaluating disease status. Staging examinations will take place every three months after study inclusion during the treatment course with cytoreductive chemotherapy (Figure 1). The total concentration of isothiocyanates (sulforaphane) in urine will serve as a monitoring parameter for the evaluation of patient compliance. Additionally, the overall survival rate will be documented.To evaluate the quality of life of the study participants, questionnaires (European Organisation for Research and Treatment of Cancer (EORTC) Quality of Life Questionnaires (QLQ-PAN26, QLQ-C30) will be completed at every follow-up visit (3, 6, and 12 months after patient inclusion), in addition to the evaluation of a patient diary kept to document the regular intake and amount of the test substances, and any observable side effects (adverse or otherwise) (Figure 1). If outcome differences between the verum and the placebo groups are detected after completion of the POUDER trial, statistical analyses will be performed in order to generate a hypothesis for a confirmatory trial on this topic.

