Biochemical analysis of serum tumor markers will take place during the first visit and for all subsequent visits, scheduled at 3-month intervals, until the end of the follow-up period. Diagnostic imaging (CT/MRI scans) will be routinely performed during the oncological follow up of the patients. If the findings of the imaging diagnostic are available, they will be included as monitoring parameters and, together with the tumor markers, will provide insight into the status of the disease. The last visit will be scheduled one year after the beginning of the trial and will serve to investigate the clinical status of the patient, as well as to compile all efficacy and safety data.

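### CA 19-9 and CEA are measured at the first visit, but the stated group comparison names no baseline covariate, which gives up precision at 20 per arm

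*Protocol article*

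**What the plan says.** All references are to the protocol article.

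- **Measurement.** *Trial interventions*: "Biochemical analysis of serum tumor markers will take place during the first visit and for all subsequent visits, scheduled at 3-month intervals". *Outcome measures* names the two markers, CA 19-9 and CEA, as parameters of disease status. A baseline value is therefore collected by design.
- **Comparison.** *Data management and statistical analysis*: for continuous parameters, descriptive P-values from a t-test or a Mann-Whitney U-test "comparing the treatment groups will be given, together with the corresponding 95% CI". No covariate, change from baseline or repeated-measures model is named.
- **Size.** Same section: "As this is a pilot study, no sample size calculation was performed", and "A sample size of 20 patients per study group has been deemed sufficient for the study objectives".
- **Allocation.** *Randomization and blinding*: 1:1 in permuted blocks. No stratification by a baseline variable is described.
- **Quality of life.** *Outcome measures*: the two EORTC questionnaires "will be completed at every follow-up visit (3, 6, and 12 months after patient inclusion"), with a pointer to Figure 1, which is not available here.
- **Purpose.** *Trial objectives*: the principal question is whether the daily intake is possible. *Outcome measures*: group comparisons serve to generate a hypothesis for a confirmatory trial.

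**The concern.** The named two-sample tests have no place for a baseline covariate, although one is measured at no extra cost. Patients with advanced disease may start with different marker levels, and nothing described in the design balances those levels between two groups of 20. If a patient's later value tracks the first one, part of the spread at follow-up is already known at entry and could be removed from the comparison.

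Two things are at stake. The confidence intervals, which are the useful product of a pilot meant to inform a confirmatory trial, are wider than they need to be. And if the arms happen to differ at entry, the unadjusted estimate carries part of that difference with it. For quality of life the same adjustment is possible only if a questionnaire is completed before treatment starts.

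**Working it through.** The article gives no effect size, SD, alpha or power, so there is no stated figure to reproduce. The check concerns precision, in units of the SD of the (log) marker.

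**Inputs.** From the article: n = 20 per arm, 95% confidence level (taken as two-sided). Assumed: the correlation ρ between baseline and follow-up, shown from 0.3 to 0.8; equal SD in both arms; all 20 per arm measured at the visit.

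**1. Chance imbalance at entry.** SE of the standardised baseline difference = √(2/20) = 0.316 SD.
- P(imbalance above 0.25 SD) = 2·[1 − Φ(0.25/0.316)] = 43%.
- P(imbalance above 0.5 SD) = 2·[1 − Φ(0.5/0.316)] = 11%.

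**2. What an unadjusted comparison of visit values carries.** Given an imbalance d, the estimate shifts by ρ·d. At ρ = 0.7 and d = 0.5 this is 0.35 SD. The rejection rate of a nominal two-sided 5% test, under no effect and given that imbalance, follows from:
- critical value 1.96 × 0.316 = 0.62
- conditional SE √(1 − 0.49) × 0.316 = 0.226
- rate about 1 − Φ((0.62 − 0.35)/0.226) = 12%

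At d = 0.25 the same calculation gives 2.5%, below the nominal level. Over all randomisations the rate is 5%, so the test is valid on average. The problem is conditional on the imbalance that actually occurred.

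**3. Precision.**
- Unadjusted half-width = t(0.975; 38) × √(2/20) = 0.64 SD.
- Adjusted half-width = t(0.975; 37) × √(1 − ρ²) × √(2/20) × √(1 + 1/36). The last factor is the expected cost of estimating the slope.
- Large-sample variance factor: 1 − ρ² adjusted, 2(1 − ρ) for change from baseline, 1 for visit values.
- Equivalent unadjusted n per arm = 20/(1 − ρ²).

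| ρ (assumed) | variance reduction ρ² | adjusted half-width (SD) | equivalent n per arm | variance factor: adjusted | variance factor: change score |
|---|---|---|---|---|---|
| 0.3 | 9% | 0.62 | 22 | 0.91 | 1.40 |
| 0.5 | 25% | 0.56 | 27 | 0.75 | 1.00 |
| 0.7 | 49% | 0.46 | 39 | 0.51 | 0.60 |
| 0.8 | 64% | 0.39 | 56 | 0.36 | 0.40 |

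At ρ = 0 adjustment would cost a little: 0.65 against 0.64 SD.

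**4. How many patients the later visits may hold.** *Background* gives a median survival of 4 to 6 months for the disease in general. If survival were exponential with that median (an assumption), the number alive per arm would be 20 × 0.5^(t/median): about 12 to 14 at month 3, 7 to 10 at month 6, and 2.5 to 5 at month 12. With 12 to 14 per arm the SE of a baseline difference is √(2/12) = 0.41 to √(2/14) = 0.38 SD. All half-widths in step 3 would widen accordingly, and the relative gain from adjustment is most usable at an early visit.

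**The case against.** The strongest case on the other side is that this is a feasibility pilot. P-values are labelled descriptive, no alpha is set, and randomisation keeps the simple test valid on average. The gain rests on a correlation that the article does not give, and at 0.3 it is negligible. Later visits may have few survivors, and there deaths, the replacement of dropouts and the removal of their data matter more than covariate adjustment, which cures none of them. All of this stands, and it sets the severity. It does not remove the point: the article names its test, so this is a stated method that can be improved with data already collected.

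A reader might also infer more than the text supports:

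- **That the tests certainly ignore the baseline.** The article does not say whether visit values or changes are compared. A change score would use the baseline. The table shows, however, that change beats visit values only when ρ exceeds 0.5 and does not beat adjustment in large samples, so naming the adjusted model helps either way.
- **That the test is chosen after seeing the data.** The clause about the nature of the data governs the choice between mean with SD and median with IQR. The sentence on the tests does not repeat it.
- **That a marker difference at month 3 could not be told from one present at entry.** The entry value is measured and can be tabulated beside it.
- **That baseline differences would exceed any treatment effect.** The article gives neither an effect nor a marker variance, and an imbalance above 0.5 SD has only an 11% chance.
- **That quality of life has no baseline.** The sentence speaks of follow-up visits and points to Figure 1. Its list is not clearly the full visit schedule, since marker visits run every 3 months and month 9 is absent from it. A questionnaire at inclusion is not excluded.

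**Conclusion.** The point holds as a low-severity improvement to a stated analysis. The article collects baseline CA 19-9 and CEA but names a two-sample comparison without a baseline covariate, and it describes no stratification that would balance the markers. The comparison is not invalid; it is less precise than the data allow, and it leaves any chance imbalance in the estimate.

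The size depends on the assumed correlation: almost nothing at 0.3, a quarter of the variance at 0.5, and nearly two thirds at 0.8. These figures also assume 20 measured patients per arm, which may not hold even at month 3. The quality-of-life part is a query that Figure 1 can settle, not a finding.

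**What to change.** In *Data management and statistical analysis*, replace the unadjusted test as the main marker comparison:

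- Compare log CA 19-9 and log CEA at one named early visit, for example month 3, by analysis of covariance with arm and log baseline value.
- Report the adjusted ratio of geometric means with its 95% CI.
- Keep the t-test or Mann-Whitney result as a supplement, stating whether it uses visit values or changes.
- State how many patients per arm contribute, and say that the comparison is among patients with a value at that visit. Deaths, replacements and removed data need their own handling.

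Query: confirm from Figure 1 whether the EORTC questionnaires are completed at inclusion. If they are, say so in *Outcome measures*. If not, add them at the existing first visit before the first capsule, and adjust for that score in the same way. A missing baseline questionnaire cannot be recovered later, so this should be settled before further patients start.

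Cost: a change of analysis wording, slightly more analysis work and one degree of freedom (38 to 37). If the query is answered in the negative, it also costs one questionnaire set at a visit that already takes place. No extra patients are needed.
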